
**Figure 1 fig1:**
[figure not shown]
Flow diagram of this study.

### Participants and recruitment

2.2

#### Sample size calculation

2.2.1

According to the most detailed research conducted in Spain, the estimated prevalence of FM among the population is 2.4%. Specifically, among women of 40 to 49 years of age, the prevalence is 8.4%, whereas for women between 50 and 59, it stands at 6.7% (30). With this data, we will set the expected prevalence in 7.5% (mean value between 8.4% and 6.7%) and calculate sample size with the *Z*-level of confidence (1.96), the expected prevalence *p* (7.5) and the precision (*d*, calculated as *P*/2) the following formula:
$$n=\frac{Z^{2}P\left(1-P\right)}{d^{2}}$$
With this calculation, a 95% confidence interval (CI) with an α level of 0.05 and an additional 10% based on an estimation of patients’ withdrawal, a minimum of 206 participants is required. The statistical power will be set at 0.80 (*β* = 0.2).

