### Study design

2.1

This is a randomized, prospective, low-interventional, double-blinded and placebo-controlled clinical trial. This study will be performed on adult women who meet ACR diagnostic criteria for FM (FM group), along with age-matched healthy volunteers (CONTROL group). The double-blinded, placebo-controlled, randomized experiment will be conducted by using extra virgin olive oil (EVOO) as treatment and olive oil (OO) as placebo, being under nutritional intervention in adherence to a Mediterranean diet supplemented with one of the olive oils for 6 months since the first sample collection. The participants will be assigned to each group randomly, using the balanced block randomization method. Briefly, once participants have been chosen for project enrollment, they will be tagged with an ordinal numeric code with three numbers by an employee from the company not related with the project nor the laboratory. This same employee will decide the codification of treatment (EVOO) and placebo (OO) groups, by assigning them an “A” or a “B” letter. Then, a second employee neither related with project or lab workflow, will randomly allocate these codes to 8-individuals blocks composed by 4 patients and 4 healthy volunteers. These blocks will be assigned to a treatment group by following the pattern ABBAABBA. In this process, this second employee will only have access to the date and time in which the participation form was completed as a unique identifier, as well as the condition of the participant: patient (FM) or healthy volunteer (CONTROL). This process will ensure that no one can link any code to its health condition, neither to participants’ data. Both processes will be reflected in patients’ database and documented in a password encrypted word file that will be also kept physically in a key-protected drawer during the entire project. The blinding method will be maintained until the data have been fully analyzed, and once this information is required to write the scientific communications that will be generated. As a result, both, patients and researchers will be fully blinded about treatment to be taken and health conditions from each participant code. Furthermore, by following the balanced block randomization method, the treatment and placebo group will comprise the same number of patients and healthy individuals. The study will span a total duration of 12 months, during which four blood and stool samples will be collected from each participant: the first before nutritional intervention (T_0_), the second after 3 months of nutritional intervention (T_1_), the third at the conclusion of the six-month nutritional intervention (T_2_) and the fourth 6 months after the end of the intervention (T_F_). This final timepoint have been included to check whether the identified biomarkers that response to nutritional intervention would change back again to the baseline, indicating a strong dependance between nutritional habits and these specific biomarkers. Figure 1 illustrates the workflow that will be followed in this study.

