## Discussion

3

FM is a chronic condition that is characterized by pain and for which there is still no precise molecular diagnosis in the healthcare community. Therefore, the main objective of FIBROKIT is to develop a panel of specific biomarkers that can facilitate precise diagnosis and monitoring of the disease. This research will enhance our understanding of the role of oxidative stress, mitochondrial metabolism, intestinal microbiota and inflammation in the pathophysiology of FM. This study introduces a novel approach by designing a comprehensive panel of specific biomarkers for the disease which has not been previously documented. Furthermore, the inclusion of 250 patients represents a significantly larger sample size compared to similar studies, which will help to find relevant results with a strong statistical significance and power. The main goal and greatest challenge of FIBROKIT is the transfer from omics platforms to a group of proteins and microorganisms to be measured by an easy and reproducible wet-lab technique.

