
The main study limitation is the marked sex bias. However, this is a predefined bias based on the preponderance of females among FM sufferers. Other study limitations are related to participants’ performance. For instance, self-questionnaires are widely used for nutritional follow-up and health assessment, but it is difficult to determine whether participants are being honest. Additionally, participants’ adherence to the nutritional intervention will be a significant obstacle, as a 1 year study requires significant commitment. Finally, as a multicenter study, coordination of logistical and clinical appointments is presumably a difficult task, and special attention will be required over the course of the project.

In summary, FIBROKIT will be the first study in FM patients to enroll more than 200 patients for biomarker discovery research. At the end of the project, it will be assessed whether plasma and feces may be considered suitable samples in which to look for a differential signature between FM patients and healthy controls. Furthermore, biomarkers’ identification will shed light on molecular diagnosis of FM, as well as will provide potential useful therapeutic targets to deepen in the field of personalized medicine for these patients. Whether theses biomarkers will be applied in clinical practice will need further research and clinical trials with drugs and non-pharmacological therapies.

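### The sample size comes from a prevalence-survey formula that sizes neither planned comparison, the stated 80% power is tied to no effect, and the Discussion counts participants as FM patients

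*Protocol article*

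**What the plan says.** Section 2.2.1 (Sample size calculation) starts from published Spanish prevalences by age band: "we will set the expected prevalence in 7.5% (mean value between 8.4% and 6.7"%). It applies n = Z²P(1−P)/d², with Z = 1.96 and "the precision (*d*, calculated as *P*/2"). It cites "a 95% confidence interval (CI) with an α level of 0.05", adds 10% for withdrawal and concludes that "a minimum of 206 participants is required. The statistical power will be set at 0.80".

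Section 2.2.2 plans to recruit 250 participants. Section 2.1 (Study design) randomises in "8-individuals blocks composed by 4 patients and 4 healthy volunteers" and states that both oil groups will hold equal numbers of patients and healthy women.

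Section 2.4.6 (Statistical analysis) plans a t-test or Mann–Whitney test for FM vs CONTROL at T0. For treatment vs placebo it plans a pre-post ANCOVA with multiple comparison correction.

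The Discussion says that "the inclusion of 250 patients represents a significantly larger sample size compared to similar studies" and expects strong significance and power from this. It closes with the claim that "FIBROKIT will be the first study in FM patients to enroll more than 200 patients for biomarker discovery research".

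**The concern.** The formula answers a question that the trial does not ask. It gives the number of people to survey so that a population prevalence near 7.5% is estimated to within half its value. Here the proportion with FM is set by the recruitment blocks, and the aims in the Introduction are a panel that separates FM from healthy women and the response of that panel to nutrition.

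Power of 0.80 needs a hypothesis, an effect, a standard deviation and a test. The calculation has none of these, so a reader cannot tell what the trial has 80% power to detect. The Discussion then builds a claim of power, and a claim to be the first study of its size, on a count of FM patients about twice what the design yields. The paragraph in Section 2.2.1 is the only quantitative justification of the trial's size in the document.

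**Working it through.** **1. The plan's own figure.** Inputs from Section 2.2.1: Z = 1.96, d = P/2, 10% added.

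- P = 7.5% (as stated): 1.96² × 0.075 × 0.925 / 0.0375² = 189.5; × 1.1 = 208.5.
- P = 7.55% (the exact mean of 8.4% and 6.7%): 188.2; × 1.1 = 206.98.
- P = 7.6% (that mean rounded up): 186.8; × 1.1 = 205.5, so 206.

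The stated 206 is therefore reproduced to within rounding of P.

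**2. What the formula delivers.** It gives a 95% confidence interval of 7.5% ± 3.75 points for one proportion. It has no term for β, for a difference between groups or for a standard deviation. Changing the power from 0.80 to any other value would leave 206 unchanged.

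**3. Head count.** Blocks of 4 + 4 give a 1:1 mix, so 250 / 2 = 125 with FM. Equal oil groups give 125 / 2 = 62 to 63 FM patients per oil. At the stated minimum of 206 the counts are 103 and 51 to 52. More than 200 FM patients would need more than 400 participants at this mix.

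**4. What 250 can detect.** The document gives no effect size or SD for any endpoint, so no corrected N can be derived. What can be stated is the smallest standardised difference detectable with 80% power at two-sided 0.05. The normal approximation is (1.960 + 0.842) × √(1/n₁ + 1/n₂):

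- 125 vs 125: 2.802 × 0.1265 = 0.354
- 62 vs 63: 2.802 × 0.1789 = 0.501

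The exact noncentral-t values are slightly larger and are used below. ANCOVA multiplies the detectable difference by √(1 − ρ²). With ρ = 0.5 between T0 and follow-up (assumed) the factor is 0.866.

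| Comparison | n per group | Unadjusted | ANCOVA, ρ = 0.5 |
|---|---|---|---|
| FM vs CONTROL at T0 | 125 / 125 | 0.36 SD | not applicable |
| EVOO vs OO within FM | 62 / 63 | 0.51 SD | 0.44 SD |
| The same after 10% loss | 56 / 56 | 0.53 SD | 0.46 SD |
| EVOO vs OO, all participants | 125 / 125 | 0.36 SD | 0.31 SD |

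The ANCOVA figure depends on the assumed correlation. For the oils within FM before losses it is 0.48 SD at ρ = 0.3 and 0.36 SD at ρ = 0.7.

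**5. One power figure cannot cover both comparisons.** For a true difference of 0.3 SD (assumed), power is 66% for FM vs CONTROL. For the oils within FM it is 38% unadjusted, or about 48% by ANCOVA with ρ = 0.5.

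**6. Multiplicity.** The figures above are for a single test at 0.05. As an illustration only, a Bonferroni threshold of 0.05 / 500 = 0.0001 (both the rule and the 500 proteins are assumed) raises FM vs CONTROL to 0.61 SD. It raises the oils within FM to 0.87 SD unadjusted, or 0.76 SD by ANCOVA with ρ = 0.5.

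**The case against.** Four points can be made for the plan.

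*The number is not miscalculated.* A reader who puts in P = 7.5% gets 208.5 and might infer that 206 is an arithmetic error. The document does not support that. It describes P as the mean of two values whose exact mean is 7.55%, and P between 7.55% and 7.6% leads to 206. The gap of up to three participants is rounding, and the 250 planned exceeds every variant. This part of the defence stands in full.

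*The power is undefined, not false.* A reader might infer that the trial lacks 80% power or is underpowered. That does not follow. The design does have 80% power for some differences, as the table shows. What can be said is that the stated 0.80 is attached to nothing.

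*The oil contrast is not limited to FM, and it is adjusted.* Section 2.4.6 speaks only of treatment vs placebo, and healthy women are randomised too. Restricting to FM is a reasonable reading but not a stated one, and quoting only unadjusted figures would understate the planned ANCOVA. Both readings and both methods are therefore shown.

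*The word patients is used loosely.* The article elsewhere uses it for participants in general, and the Abstract correctly says more than 200 participants. That explains the slip. It does not rescue the closing sentence, which presents the count as enrolment in a study of FM patients and rests a claim of priority on it.

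**Conclusion.** The point holds as a wrong choice of method and a misstated count. The prevalence formula sizes neither planned comparison, so 206 gives no support to the trial's aims. The power of 0.80 enters no part of the calculation and is not shown for this design. The Discussion overstates the number of FM patients about twofold: 250 or more than 200, against about 125.

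Nothing here shows that 250 is too few. Whether it suffices depends on effects that the document does not state. The head counts follow directly from the blocks. The detectable differences rest on a single two-sided test at 0.05, approximately normal outcomes and, for ANCOVA, an assumed correlation of 0.5. They grow once the planned multiplicity correction is applied.

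**What to change.** Keep N = 250.

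1. In Section 2.2.1, remove the prevalence formula and the bare 0.80. State what 250 participants can detect with 80% power at two-sided 0.05:
   - FM vs CONTROL: about 0.36 SD.
   - EVOO vs OO within FM: about 0.51 SD unadjusted, 0.44 SD by ANCOVA, and 0.46 SD by ANCOVA after 10% loss.
   - EVOO vs OO across all participants, if that is the intended contrast: about 0.36 SD unadjusted or 0.31 SD by ANCOVA.
2. Label the baseline correlation of 0.5 as an assumption, say which oil contrast is meant, and state that all these differences increase under the multiplicity correction.
3. Do not add a precision figure for the area under the ROC curve of the diagnostic panel. A standard-error formula for a fixed marker would overstate the precision of a panel selected from the same women.
4. In both Discussion sentences, write 250 participants, about 125 of them with FM. Withdraw or re-base the priority claim accordingly, and delete the expectation of strong statistical significance and power.

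The cost is one rewritten paragraph and a few sentences. Recruitment, arms and analysis do not change, and the stated figures become less favourable.

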#### Inclusion criteria

2.2.2

A total of 250 participants will be recruited for the study through an online survey launched across FM associations and social media in order to effectively reach a larger pool of potential participants. To be eligible, the participants must meet the following inclusion criteria:Age range of 40 to 59 years, since these women are the most affected population group (30).Maintenance of a sedentary lifestyle and adherence to a balanced diet following the principles of the Mediterranean diet, in order to limit the observed changes to those related with nutritional habitsConfirmed FM diagnosis by a healthcare professional according to 1990 ACR criteria.

Exclusion criteria for the study are as follows:Individuals outside the age range of 40 to 59 years.Participants who have engaged in structured or planned physical activity in the last month, such as medium or high intensity directed classes or scheduled aerobic/anaerobic exercise for more than 2 days a week.Individuals who are either underweight (BMI <18.5) or severely obese (BMI >35.9).Those diagnosed with any form of cancer, cardiovascular disease (e.g., atherosclerosis, cardiomyopathy), autoimmune diseases (e.g., lupus, celiac disease, thyroiditis) or metabolic disorders (e.g., diabetes, metabolic syndrome).Participants who have undergone pharmacological treatment with non-steroidal anti-inflammatory drugs, analgesics, antidepressants or antioxidants in the month preceding the study.Consumption of alcohol exceeding 12 g/day, as specified in the Mediterranean diet.

Before the beginning of the project, participants will complete an informed consent form and a patients’ information datasheet (Supplementary file S1) that have been approved by the Ethical Committee for Research with Medications (CEIM) at the Quirónsalud-Catalunya Hospital Group (protocol code IDI-20210749, approval record No. 01/2022).

#### Adherence

2.2.3

To ensure adherence, each participant will be given individualized attention. The assigned nutritionists will maintain regular contact with the participants to assess their progress with the intervention, following a contact plan based on two phone calls per month. In addition, a phone line and a specific mail inbox ([contact]) will be created for queries, complaints and management of sample collection appointments. All the participants experiencing adverse event such as gastrointestinal complications, constipation, acute diarrhea or severe weight loss or gain will be immediately evaluated by nutritionists and proposed for withdrawal if those effects are somehow related to the nutritional intervention. Besides, the phone line will be uses for instant messaging communication with patients, to send them reminders about clinical appointments, solve some doubts about menus and olive oil consumption or adverse events assistance. A proactive communication plan has been designed to collect information regarding the reasons for the participants’ missed appointments, inactivity, or withdrawal. Additionally, in case of withdrawal or sample collection missing, the data collected will be used in the analysis, although upcoming datapoints will be unavoidably missed. Even though we will analyze a fully completed group of 250 participants at starting point (T_0_), the groups are expected to decrease while the project goes on, so patients with missing data will not be included in upcoming timepoints analysis.

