
#### Statistical analysis

2.4.6

The statistical analysis will be performed in RStudio, using R v3.6.2 base packages. First, data distribution will be assessed by using the Kolmogorov–Smirnov test, which evaluates the null hypothesis that data correspond to normal distribution. In that case, in analyses of CONTROL vs. FM groups T_0_, parametric tests such as the unpaired student’s *t*-test and the Pearson correlation test will be used to investigate mean differences and correlation between quantitative variables, respectively. If data do not display normal distribution, the Mann–Whitney *U* test and the Spearman correlation non-parametric test will be applied for this purpose. Additionally, for comparison among groups when depicting nutritional intervention influence with treatment vs. placebo, pre-post analysis through analysis of covariance (ANCOVA) with multiple comparison correction will be used, since it has been shown to be the most powerful analysis for this experimental design (39). In all cases, the significance level (*α*) will be established at 0.05 so that null-hypothesis will be rejected when the *p*-value is <0.05. Tables will be used as preferred format to show descriptive data, such as demographic characteristics, stacked bar charts and/or pie charts will be used to represent distributions, bar charts and/or box and whiskers plots will be applied when showing differences in mean among groups and, finally, violin plots, volcano plots and additional statistical representations will be the format to show distribution and significance in the values found in each group.

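### The missing-data rule treats one missed sample like withdrawal and, read literally, excludes later samples that the planned ANCOVA could use

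*Protocol article*

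**What the plan says.** Section 2.2.3 (Adherence) sets one rule for two events: "in case of withdrawal or sample collection missing, the data collected will be used in the analysis, although upcoming datapoints will be unavoidably missed". It then says that "we will analyze a fully completed group of 250 participants at starting point", that the groups are expected to shrink afterwards, "so patients with missing data will not be included in upcoming timepoints analysis".

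Three other statements bear on this:

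- Section 2.1 (Study design) fixes a 12-month schedule "during which four blood and stool samples will be collected from each participant": T0, T1 at 3 months, T2 at 6 months, and T_F six months after the intervention ends.
- Section 2.4.6 (Statistical analysis) says that for treatment versus placebo "pre-post analysis through analysis of covariance (ANCOVA) with multiple comparison correction will be used".
- Section 2.2.1 (Sample size calculation) contains the only attrition figure: "an additional 10% based on an estimation of patients’ withdrawal, a minimum of 206 participants is required".

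The article describes no imputation, repeated-measures model or sensitivity analysis that would offset the rule.

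**The concern.** Later data are indeed gone once a woman has withdrawn. They are not gone after one missed collection, because her remaining visits are still scheduled. By giving both events the same consequence, the text excludes a woman who misses T1 and returns for T2 or T_F, although her blood and stool have been collected.

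The ANCOVA gains nothing from this. It regresses the value at the visit analysed on oil group and T0, and the visits in between do not enter.

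What is at stake is precision in the oil comparison, which serves the secondary objective. The loss builds up over visits and is largest at T_F, the time point meant to show whether responsive markers return to baseline.

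**Working it through.** **The plan's own figure.** The sample-size formula with Z = 1.96, P = 0.075 and d = P/2 gives 1.96² × 0.075 × 0.925 / 0.0375² = 189.5, and × 1.10 = 208.5. With P = 0.0755, the exact mean of 8.4% and 6.7%, it gives 188.2 × 1.10 = 207.0. The stated 206 is reproduced within rounding and is not in dispute. It matters here only because it supplies the 10% withdrawal allowance.

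**Inputs from the article.** 250 women at T0. Blocks hold 4 patients and 4 healthy volunteers, and "the treatment and placebo group will comprise the same number of patients and healthy individuals". That implies about 125 FM women, or 62.5 per oil.

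**Assumptions.** The article gives no missed-visit rate. I take 10% total withdrawal spread evenly over the three post-baseline visits, so the fraction remaining per visit is s = 0.90^(1/3) = 0.9655. A woman still in the study misses any one visit with probability m, independently of other visits.

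**Samples kept at post-baseline visit k** (T1: k = 1; T2: k = 2; T_F: k = 3):

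- every available sample: 250 × s^k × (1 − m)
- literal rule: 250 × s^k × (1 − m)^k

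The two agree at T1, so nothing is discarded there. Example at m = 10%: for T2, 250 × 0.9322 × 0.90 = 209.7 against 250 × 0.9322 × 0.81 = 188.8. For T_F, 250 × 0.90 × 0.90 = 202.5 against 250 × 0.90 × 0.729 = 164.0.

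| m | T2 available | T2 rule | discarded | T_F available | T_F rule | discarded |
|---|---|---|---|---|---|---|
| 0% | 233.0 | 233.0 | 0 | 225.0 | 225.0 | 0 |
| 3% | 226.1 | 219.3 | 6.8 | 218.2 | 205.4 | 12.9 |
| 5% | 221.4 | 210.3 | 11.1 | 213.7 | 192.9 | 20.8 |
| 10% | 209.7 | 188.8 | 21.0 | 202.5 | 164.0 | 38.5 |
| 15% | 198.1 | 168.4 | 29.7 | 191.2 | 138.2 | 53.1 |

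(Discarded counts are taken before rounding.)

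**Power within FM** (125 women; assumed true difference 0.5 SD; two-sided 5%; no gain from the T0 covariate):

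- m = 5%: 0.749 falls to 0.727 at T2, and 0.734 to 0.690 at T_F.
- m = 10%: 0.726 falls to 0.680 at T2, and 0.711 to 0.619 at T_F.

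**Detectable difference within FM**, 80% power, 10% missed per visit and no other loss, from d = (1.96 + 0.84) × √(2/n per oil):

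- all available, T2 or T_F: n = 62.5 × 0.9 = 56.3, d = 0.53 SD
- rule, T2: n = 62.5 × 0.9² = 50.6, d = 0.56 SD
- rule, T_F: n = 62.5 × 0.9³ = 45.6, d = 0.59 SD

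Adjusting for T0 would shrink all three by the same factor if the correlation with T0 is equal across visits.

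**Bias from the rule itself.** In a simulated ANCOVA the true effect was zero and the between-visit correlation 0.6. T1 was missed with probability 5%, except by EVOO women with a T1 value above 0.5 SD, for whom it was 10%, 20% or 30%. The T2 estimate under the rule shifted by about −0.005, −0.017 and −0.025 SD. Using all T2 samples the shift was 0.000.

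**The case against.** The strongest reply is that the sentence describes attrition and sets no exclusion rule. It follows a remark that the groups will shrink, and it calls the later data points unavoidably missed, which fits women who have left. On that reading the m = 0 row applies and no sample is discarded. This stands as a possible reading. It does not settle the matter, because a missed collection is named beside withdrawal, and later data are not unavoidably lost after one missed visit.

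A reader might also infer that the rule turns the randomised comparison into a biased completer analysis, since women with adverse effects are "proposed for withdrawal if those effects are somehow related to the nutritional intervention" and losses could therefore differ by oil. The article does not support charging that to this rule. Women who withdraw and give no further samples are absent from the later analysis under any rule for handling missed visits, so bias from their dropout would remain after the correction. Data before the gap are also kept: T1 includes everyone sampled at T1, and only at T_F does the literal rule require all four samples.

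Finally, a full analysis plan may exist and choose a different model. That is a reason not to prescribe one here. It does not excuse the sentence in section 2.2.3, which states a rule.

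**Conclusion.** The point holds in a limited form. Section 2.2.3 gives a missed sample the same consequence as withdrawal, and followed literally it excludes usable T2 and T_F samples from the oil comparison for no analytic reason.

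The cost is about 7 to 30 samples at T2 and 13 to 53 at T_F out of 250, under the assumed 10% withdrawal and 3% to 15% missed per visit. It is nil if every gap is a withdrawal. At the end of the intervention (T2) the loss of precision is modest, 0.53 to 0.56 SD in the 10% example. The increase to 0.59 SD belongs to T_F and should not be read as the cost at T2.

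Bias from the rule was at most about 0.025 SD in the scenarios tried. The primary aim, with its T0 comparison of FM and CONTROL, is unaffected. The change is worth making because it costs almost nothing. Confidence is moderate, because the wording can be read two ways.

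**What to change.** In section 2.2.3:

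1. Separate a missed visit from withdrawal, and state that a missed visit does not end sampling: the woman is still invited to her remaining scheduled collections.
2. Replace the exclusion sentence. Every randomised woman with a T0 sample is analysed in her assigned oil group at each later visit where she has a sample, using the planned ANCOVA for that time point.
3. Report the analysis of women with no missed visits as a sensitivity analysis.

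A repeated-measures model with T0 as covariate is an option for outcomes measured at T1, T2 and T_F. Its downside is reliance on data being missing at random. It should not be imposed on every outcome: section 2.4.3 lists total antioxidant capacity at T0 and T_F only, and section 2.4.5 sends the microbiota data through DESeq2.

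The cost is a change of wording. No visit is added, and the model already planned suffices.

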#### Microbiota and intestinal permeability analysis

2.4.5

Participants will collect fecal samples using the DANASTOOL sample collection kit (Danagen; Barcelona, Spain). They will use a Fe-Col^®^ Faecal sample collection paper (Alpha Laboratories; Hampshire, United Kingdom) as a stool-catch platform. The participants will scoop a small portion of stool into the provided stool tube, which contains a liquid DNA/RNA stabilization solution. Following collection, all samples will be stored in accordance with established quality standards. Since the DANASTOOL sample collection kit has a DNA/RNA stabilization solution, samples were stored at room temperature until batch analysis. DNA extraction from fecal samples will be carried out using the DANAGENE MICROBIOME FECAL DNA KIT (Danagen; Barcelona, Spain). Briefly, 1 ml of homogenized sample was transferred to a tube containing beads to ease sample disruption. Then, samples were incubated at 70°C during 10 min. After incubation step, a thorough vortexing and centrifugation steps were applied. The upper phase was then transferred to a filtering column to extract DNA by centrifugation. The extracted DNA will then be used to analyze the composition of the gut microbiota. This analysis will involve amplicon metagenomics sequencing, in which amplicons of V3–V4 regions from the 16S rDNA will be sequenced using the Illumina MiSeq platform at HelixBioS (Madrid, Spain) facilities. A tagging and barcoding process suitable for Illumina technology will be conducted, according to manufacturer instruction. Each sample will undergo individual quantification, pooling, washing and titration using qPCR. The sequencing will be performed on the MiSeq platform with a fragment size ranging from 2 × 250 to 2 × 300, with the aim of generating 150,000 to 200,000 reads per sample. We will set the minimal number of reads per sample at 50,000 as quantity threshold, and Phred Score at Q30 as quality threshold. Samples with an average trimmed read length below 280 bp will be discarded. All these quality control procedures will be applied through MultiQC software (36) and sequencing results will be analyzed with USEARCH V11.1. Briefly, the reads will be cleaned using the UCHIME algorithm to eliminate “singletons” sequences (those that only had one copy in the total sequences), chimera sequences and possible artifacts. ZOTUs clustering will be carried out using the UNOISE algorithm at 99% identity (similarity). The sequences will be then aligned against the taxonomic database developed for the study of the intestinal microbiota, HUMAN GUT 16S (HelixBioS), with an alignment cut-off point of 99% (identity) using the algorithm USE-LOCAL. The results will be finally processed with phyloseq (37) and DESeq2 (38).

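### The missing-data sentence treats one missed sample like withdrawal and, read literally, drops a returning woman from the EVOO versus OO analysis at every later visit

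*Protocol article*

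**What the plan says.** Study design (2.1) plans repeated sampling: "four blood and stool samples will be collected from each participant", at T0, T1 (3 months), T2 (6 months, end of intervention) and T_F (6 months after that). T_F is there to see whether markers that responded to the diet return to baseline.

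Adherence (2.2.3) sets out what happens when data are incomplete. First: "in case of withdrawal or sample collection missing, the data collected will be used in the analysis, although upcoming datapoints will be unavoidably missed". Then it describes the expected course: "we will analyze a fully completed group of 250 participants at starting point (T_0_), the groups are expected to decrease while the project goes on". It ends with the operative rule: "so patients with missing data will not be included in upcoming timepoints analysis".

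Statistical analysis (2.4.6) says that for treatment against placebo "pre-post analysis through analysis of covariance (ANCOVA) with multiple comparison correction will be used". The T0 comparison of CONTROL with FM is a separate analysis.

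No section says what happens to a participant who misses one collection and then attends a later one.

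**The concern.** Two different situations share one rule. A woman who withdraws gives no later samples, so nothing can be done at later visits. A woman who misses one collection and stays in the study can still give T2 and T_F samples, so for her the premise that later data are unavoidably lost is false. The exclusion is nevertheless attached to the patient and to upcoming timepoints, not to the missing value.

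Two things are at stake in the EVOO versus OO comparison:

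- **Precision.** Usable follow-up values would be set aside, most of all at T_F, where two earlier follow-up visits can trigger the exclusion.
- **Selection.** Inclusion at T2 or T_F would depend on a complete earlier record, which is a post-randomisation event. If missing T1 is related both to the oil and to the marker, the randomised comparison is no longer protected. A change in means from T0 to T2 to T_F could also partly reflect who was kept in.

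**Working it through.** **Step 1: the wording.** Three features favour the literal reading.

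- Withdrawal and a missing sample are named as alternatives. The same section's communication plan also lists missed appointments, inactivity and withdrawal separately, so the plan expects women who miss a visit without leaving.
- With four scheduled collections, missing T1 does not prevent T2 or T_F.
- A rule to analyse whatever is available would omit the missing value. This rule omits the patient from the visits that follow.

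**Step 2: the plan's only attrition figure.** Sample size calculation (2.2.1) includes "an additional 10% based on an estimation of patients’ withdrawal, a minimum of 206 participants is required". With Z = 1.96 and d = P/2, n = Z²P(1−P)/d². For P = 0.0755 this is 188.2, and × 1.10 = 206.98 (206 if truncated). For P = 0.075 it is 189.5, and × 1.10 = 208.5. The figure reproduces closely. It matters here only as the source of the 10% withdrawal allowance.

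**Step 3: illustrating the loss.** Inputs from the article: 250 women at T0 and 10% withdrawal. Assumptions: withdrawal is spread at a constant rate over the three follow-up visits, so a fraction 0.9^(k/3) remains at visit k (T1, T2, T_F = 1, 2, 3); each woman still enrolled misses any given visit with probability m, independently across visits. The article gives no value for m, so a range is shown.

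- Every attended visit used: N = 250 × 0.9^(k/3) × (1−m)
- Literal rule: N = 250 × 0.9^(k/3) × (1−m)^k

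For m = 5% at T2: 250 × 0.9^(2/3) = 233.0; × 0.95 = 221; × 0.95² = 210; difference 11. At T_F: 225 × 0.95 = 214; 225 × 0.95³ = 193; difference 21.

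| m | T2, all attended | T2, literal rule | Lost | T_F, all attended | T_F, literal rule | Lost |
|---|---|---|---|---|---|---|
| 0% | 233 | 233 | 0 | 225 | 225 | 0 |
| 3% | 226 | 219 | 7 | 218 | 205 | 13 |
| 5% | 221 | 210 | 11 | 214 | 193 | 21 |
| 10% | 210 | 189 | 21 | 202 | 164 | 38 |

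T1 is unaffected, because T0 is taken as complete.

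**Step 4: effect on the standard error.** The ratio of standard errors, literal rule to all attended visits, is (1−m)^(−(k−1)/2). At T2 it is 1.015, 1.026 and 1.054 for m = 3%, 5% and 10%. At T_F it is 1.031, 1.053 and 1.111. The withdrawal rate cancels out. If the same women tend to miss repeatedly, the loss is smaller than shown.

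**The case against.** The strongest reply is that nothing is actually thrown away. The article says collected data will be used, and the reference to shrinking groups describes ordinary attrition. On that reading the last sentence says only that women who have left have no later data to analyse. The reading is possible, and it means that discarding attended samples is inferred from the wording, not stated. It fits poorly with a rule that names a missing sample separately from withdrawal and excludes the patient from upcoming timepoints. Even if it is what was meant, the text leaves the returning woman unresolved.

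Four further points against a stronger reading stand:

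- A reader might infer that a stool sample failing sequencing quality control also triggers exclusion. The Microbiota section's threshold ("We will set the minimal number of reads per sample at 50,000 as quantity threshold") applies per sample, and a failed sample was still collected. Nothing there removes the participant.
- A reader might infer that a missing stool sample removes later blood results. The rule is not written per assay, but no section states this, so no number should be put on it.
- A reader might compare the shrinking set with 206. That figure already includes the withdrawal allowance, and it comes from a formula for the precision of a prevalence. It is no benchmark for EVOO versus OO.
- A different, smaller set at each visit arises under any available-data analysis with dropout. Only the part due to excluding returning women comes from this rule.

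Detailed missing-data methods may sit in an analysis plan that is not shown; their absence is not the point. The point is a rule that the article does state.

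**Conclusion.** The point holds as a should-fix. As literally written, section 2.2.3 would exclude a returning woman from later EVOO versus OO analyses, with no scientific gain.

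The size depends wholly on how many women miss a visit and come back, which the article does not say. It is nil if all missingness is permanent dropout. Under the stated assumptions (10% withdrawal, 3% to 10% missed per visit) it is about 7 to 21 women at T2 and 13 to 38 at T_F, with standard errors about 1.5% to 5% larger at T2 and 3% to 11% larger at T_F. The direction and size of any selection bias cannot be derived from the documents.

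A reader might infer that the trial's main result is at risk. It is not. The Introduction makes the diagnostic panel the primary focus and nutrition the secondary objective, and the CONTROL versus FM comparison is made at T0, before this rule can act.

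**What to change.** Replace the final sentence of section 2.2.3 with:

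> Every randomised participant is analysed in her allocated arm at every visit for which that assay result exists; a missing result at one visit or in one assay does not remove her other results.

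Limit the remark about unavoidable loss of later data to participants who have withdrawn. Keep the planned ANCOVA, run at each follow-up visit on all available pairs of T0 and follow-up values, and report the number analysed per arm and visit.

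A repeated-measures model is optional for markers measured at T1, T2 and T_F. It is not needed to correct the rule. It would not suit total antioxidant capacity, which section 2.4.3 plans only at T0 and T_F, or the microbiota counts, which section 2.4.5 sends to DESeq2.

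The cost is a wording change, with no extra participants, visits or assays. It should be made before follow-up data are analysed and while the blind is intact.
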